### Economic evaluation

The economic evaluation will be performed as a cost-effectiveness analysis with the costs per prevented foot ulcer as the primary outcome. A cost-utility analysis will be performed with the costs per QALY as outcome. Both will be performed from a societal perspective. Considering the time horizon of 18 months, we will discount the effects and costs during the second year of follow-up. The Dutch Government recommends a discount rate of 4% for costs and 1.5% for effects [28].

Given the societal perspective, data will be collected on direct medical and non-medical costs as well as indirect non-medical costs. Direct medical costs include, for example, the costs of foot care, the thermometer and care provided by other health care professionals (general practitioner, medical specialist). Direct non-medical costs include, for example, out-of-pocket expenses by patients for travel to and from health care providers, private household assistance, and over-the-counter medication. Indirect non-medical costs reflect the costs of productivity loss due to sick leave from work or lower productivity while at work. Costs will be calculated as the product sum of resource volume data and their respective unit costs, as described in the Dutch manual for costing in health care research [29]. Costs associated with productivity loss will be based on the friction cost method, applying the actual mean friction period in the base year of the study. After price-indexing with general yearly consumer price indices, all costs will be expressed in euros for the base year 2015.

Incremental cost-effectiveness ratios will be calculated as the extra costs per additional patient without foot ulcer and the extra costs per QALY gained. To account for sampling variability, group differences will be assessed by calculating the 95% confidence intervals after correction for bias and using accelerated non-parametric bootstrapping. If enhanced therapy does not dominate usual care, results will be displayed graphically with cost-effectiveness acceptability curves for willingness to pay values up to €100,000.

Health utilities associated with the scoring profiles on the EQ-5D-3 L are available through the cross-walk value sets from the www.euroqol.org website and will be used to derive a QALY estimate for each patient. This QALY will be calculated as the product sum of health utilities and the lengths of the periods in-between successive measurements. In case of missing assessments, the last observation will be carried forward. Sensitivity analyses will be performed for different (Dutch and UK population-based) health-utility scoring algorithms used to derive QALYs as well as for different discounting rates to reflect time preference.

A subgroup analysis of cost-effectiveness and cost-utility will be performed by level of adherence to temperature monitoring.

The cost consequences of monitoring foot temperature at home, such as by the use of the measurement device and intensified monitoring costs, may affect health care budgets. A budget impact analysis (BIA) will be carried out from governmental, health care provider, and insurer perspectives. The governmental perspective is chosen to help setting priorities in health care optimization while simultaneously considering the wider implications of stimulating enhanced therapy for diabetic patients at a high risk of ulcers beyond the health care sector. The provider perspective is chosen to support local decisions on economies of scale and affordability. The insurer perspective is chosen to assess the net financial consequences of offering intensified monitoring to high-risk patients who have a history of ulceration, which may help to shift health care use from the second to the first echelon. For this study, the BIA will be conducted using a decision-tree model developed in Microsoft® Excel. The BIA will be performed according to the ISPOR Task Force principles [30].

Finally, a scenario analysis will be carried out, simulating three implementation scenarios against the base scenario (usual care): (1) immediate use of the device, (2) gradual use (an absolute 25% yearly increase of patients in the target group using the device), and (3) partial use (up to 70% of the whole target population). Sensitivity analyses will be applied for the level of adherence to temperature monitoring and for a potential shift from podiatric to pedicure foot care. The BIA will have a time horizon of 4 years. Results will be reported for successive calendar years.

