### Hypothesis

We hypothesize that enhanced therapy, which includes at-home infrared temperature monitoring of the foot, results in a significantly lower proportion of patients with foot ulcer recurrence, is cost-effective and saves costs per quality-adjusted life years (QALYs) gained when compared to usual care. The hypothesis is based on superiority of enhanced therapy compared to usual care.

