### Sample size calculation

Based on the results of a footwear efficacy trial that was largely conducted in the same centers as this trial and also assessed patients with a history of foot ulceration [24], we anticipate for the usual-care group that 44% of participants will develop a recurrent foot ulcer during 18 months’ follow-up. Using a conservative estimate from three previous trials on the effectiveness of at-home foot temperature monitoring [15–17], we anticipate that 28.6% of participants in the enhanced therapy group will develop a recurrent foot ulcer in 18 months; this represents a 35% effect size. With α = 0.05 (two-sided), power 80%, and based on an intention-to-treat analysis in which clinical outcome data from all included patients will be assessed, 304 eligible participants are required and will be randomly assigned.

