### Outcomes

The primary outcomes in this study are the cost (savings) per patient without a foot ulcer (i.e., cost-effectiveness) and per QALY gained (i.e., cost-utility). The primary clinical outcome is the proportion of participants with a recurrent foot ulcer on the plantar foot, apical surfaces of the toes, interdigital spaces or medial and lateral forefoot surfaces during 18-month follow-up. A foot ulcer is defined as a cutaneous erosion through the dermis without reference to time present [22, 23]. Endpoints in the study are either a foot ulcer, or 18 months of follow-up.

Secondary outcomes are the costs of therapy and of ulcer treatment, adherence to at-home foot temperature monitoring, and a multivariate risk score for ulcer recurrence.

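### The acceptability curve is dropped if enhanced therapy dominates, while a negative cost-effectiveness ratio, which does not rank results, is still calculated

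*Protocol article*

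**What the plan says.** The Outcomes section puts the primary outcomes in ratio form: "The primary outcomes in this study are the cost (savings) per patient without a foot ulcer (i.e., cost-effectiveness) and per QALY gained". The Economic evaluation section says how they are computed, with no condition attached: "Incremental cost-effectiveness ratios will be calculated as the extra costs per additional patient without foot ulcer and the extra costs per QALY gained". Sampling uncertainty is also handled unconditionally: "group differences will be assessed by calculating the 95% confidence intervals after correction for bias and using accelerated non-parametric bootstrapping".

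The acceptability curve is conditional: "If enhanced therapy does not dominate usual care, results will be displayed graphically with cost-effectiveness acceptability curves", over thresholds up to €100,000. The article does not say whether dominance is judged on the point estimates or on the bootstrap replicates.

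The Hypothesis section expects a lower proportion of patients with recurrence and that enhanced therapy "is cost-effective and saves costs per quality-adjusted life years (QALYs) gained when compared to usual care". The word dominance does not appear there, but better effect at lower cost is what it means.

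The planned sensitivity analyses address the utility algorithms ("Sensitivity analyses will be performed for different (Dutch and UK population-based) health-utility scoring algorithms used to derive QALYs") and the discount rates. They do not address sampling error.

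**The concern.** Two rules meet badly in the case the trial hopes for.

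First, the ratio is calculated in every quadrant. When costs fall and effects rise it is negative, and a larger or smaller negative value says nothing about which result is better.

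Second, in that same case the curve is omitted. It is the one stated display that combines cost and effect uncertainty and gives a probability of cost-effectiveness at each willingness to pay.

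If dominance is read off point estimates, the primary economic result could be reported as dominant with a ratio that has no usable meaning and without the probability behind it. These outcomes are primary and are meant to inform implementation, so the gap matters.

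**Working it through.** **The plan's own figure.** The Sample size calculation assumes that "44% of participants will develop a recurrent foot ulcer during 18 months’ follow-up" under usual care, against 28.6% with enhanced therapy, at two-sided α 0.05 and 80% power. With mean proportion 0.363:

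n per arm = [1.96·√(2·0.363·0.637) + 0.8416·√(0.44·0.56 + 0.286·0.714)]² / 0.154² = 151.9, so 152 per arm and 304 in total.

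The stated 304 reproduces. The article gives no precision figure for the economic outcomes.

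**The negative ratio.** Illustrative values, with net benefit = λ·ΔE − ΔC at λ = €50,000:

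| ΔC (€) | ΔE (QALY) | Ratio (€) | Net benefit (€) |
|---|---|---|---|
| -1,000 | +0.02 | -50,000 | +2,000 |
| -1,000 | +0.10 | -10,000 | +6,000 |
| +1,000 | -0.02 | -50,000 | -2,000 |

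Rows 1 and 2: the same saving with five times the effect gives a ratio nearer zero. Rows 1 and 3: a dominant and a dominated result share one ratio.

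**The missing curve, QALY outcome.** Inputs from the article: ulcer rates, 304 patients, and €5,000 to €17,000 per ulcer episode (Background). Assumptions not in the article:
- 152 per arm (equal allocation).
- QALY SD 0.3.
- Cost SD €9,000. A 36% ulcer rate with episode mean and SD both €11,000 gives √(0.36·2·11,000² − 3,960²) ≈ €8,500.
- Correlation -0.3.
- A loss of 0.1 utility for half a year per ulcer.
- Net cost differences of -€500 and -€1,500.

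Steps:
- ΔQALY = 0.154·0.1·0.5 = 0.0077, about 0.008.
- SE(ΔQALY) = 0.3·√(2/152) = 0.0344; SE(ΔC) = 9,000·√(2/152) = €1,032.
- P(ΔQALY < 0) = Φ(−0.0077/0.0344) = 41%.
- Bivariate-normal simulation of replicates at -€500 and +0.0077: 45% dominant, 14% more effective and dearer, 17% less effective and dearer, 24% less effective and cheaper.
- P(cost-effective) = Φ[(λΔE − ΔC)/√(λ²SE_E² + SE_C² − 2λρ·SE_E·SE_C)]. At €20,000: Φ(654/1,402) = 68%. At €80,000: Φ(1,116/3,217) = 64%.
- At -€1,500 and +0.015: 64% dominant; 90% cost-effective at €20,000 and 80% at €80,000.

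Range: with QALY SD 0.2–0.3 and cost SD €5,000–15,000, the dominant share is 41–54% in the first case and 57–74% in the second. With QALY SD 0.3, gains of 0.005–0.05, cost differences of -€500 to -€1,500 and cost SD €10,000–15,000, it is 0.37–0.84, although the point estimate dominates in every scenario.

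**Ulcer outcome, same cost assumptions.** ΔE = 0.154, SE = √(0.44·0.56/152 + 0.286·0.714/152) = 0.0544, so P(ΔE < 0) = Φ(−2.83) ≈ 0.2%. At -€500, about 68% of replicates are dominant, 31% more effective and dearer, and 0.2% show a worse effect. P(cost-effective) at €20,000 per ulcer-free patient is 98%. Nearly all the uncertainty is in costs.

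**What the unconditional intervals would show.** In the -€500 QALY case: -500 ± 1.96·1,032 = -€2,523 to +€1,523, and 0.0077 ± 1.96·0.0344 = -0.060 to +0.075 QALY. Both cross zero.

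**The case against.** The strongest reply is that the plan does report uncertainty. The bootstrap intervals for group differences carry no dominance condition, and in the example above both visibly cross zero. A reader might infer that uncertainty goes unreported, or that decision makers would be handed false certainty; the article does not support that. What remains is narrower: two separate intervals carry neither the cost–effect correlation nor a probability of cost-effectiveness at any threshold.

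A second reply is that dominance is undefined and the condition directly follows the bootstrap sentence. If it means dominance established across the replicates, dropping the curve loses little. That is fair, and it limits how firmly the point can be put. But a data-dependent reporting rule on a primary outcome should not rest on an undefined word.

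Third, a reader might infer that replicates would spread over all four quadrants for both outcomes. At the planning rates this fails for ulcers, the effect used in what the Economic evaluation section calls its primary outcome. The QALY case still counts, because Outcomes lists cost-utility as primary too.

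Fourth, the size rests on undocumented inputs. The planning rates and the quoted episode costs imply gross savings of 0.154·5,000 = €770 to 0.154·17,000 = €2,618 per patient, so a net -€500 presumes an intervention cost of €270 to €2,118, which the article does not give.

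Finally, replacing the ratio by net monetary benefit as primary summary would be a preference. The problem shown does not require it.

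**Conclusion.** The concern holds in limited form. The defect is a written rule, not an omission: the ratio is always calculated, and the curve is withheld if an undefined dominance condition is met. In the hypothesised outcome this leaves a ratio that does not rank results and no joint, threshold-specific uncertainty, although marginal intervals for costs and effects remain.

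The practical loss is mainly for QALYs: about 45% dominant replicates and a 64–68% probability of being cost-effective behind a point estimate of -€500 and +0.008 QALY. These figures illustrate the size under the stated assumptions and do not predict the trial's result. For ulcers, the cost interval already conveys most of what is uncertain.

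It would go too far to say that the protocol states a hypothesis of dominance. That is an inference, though a reasonable one, from fewer recurrences together with saved costs. Sample size, data collection and the clinical test are unaffected.

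**What to change.** In the Economic evaluation section:
- Delete the dominance condition. Show the acceptability curve, with the bootstrap cost-effectiveness plane, for both effects (ulcer-free patients and QALYs) whatever the quadrant, over the stated willingness-to-pay range up to €100,000. This also removes the need to define dominance as a trigger.
- State that when the point estimate is dominant or dominated, incremental costs and incremental effects are reported with their bootstrap intervals in place of a negative ratio.
- Optionally add incremental net benefit from the same replicates as a supporting summary. It need not replace the ratio as primary.

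The cost is a change of wording. The same bootstrap replicates are reused, and no data, visits or patients are added.

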#### Baseline assessment

After providing informed consent, participants will undergo a baseline assessment at their study center to confirm definitive eligibility for inclusion in the study. The following characteristics will be obtained during the baseline visit:Demographic information and disease-related characteristics (e.g., diabetes duration and control, presence of complications, ulcer history, footwear use, etc.);Peripheral neuropathy assessment:Presence of neuropathy will be assessed by measuring the loss of protective sensation by using the 10-g (5.07) Semmes-Weinstein monofilament at the plantar surface of the hallux and the first and fifth metatarsal heads of both feet [10]. Neuropathy is defined when the monofilament is not felt on two or more locations [22]A 128-Hz tuning fork held on the apex of the great toe [10]. Neuropathy is defined when the participant indicates not feeling the vibration [22]Peripheral vascular assessment by palpation of the dorsalis pedis and posterior tibial pulses of both feet, according to the PEDIS classification system [23]. If pulses are not palpable, additional assessment of peripheral vascular status will be done by measuring toe pressures or the participant’s medical record is checked for their vascular statusPresence of foot deformity will be assessed clinically. These include hammer/ claw toes, prominent metatarsal heads, hallux valgus, pes planus, pes cavus, Charcot deformity, and any amputation. A participant’s feet will be classified into one of four categories according to the severity of deformity present: no deformity, mild deformity, moderate deformity, and severe deformity [24]

If definitive eligibility has been confirmed, photographs of the plantar and dorsal surfaces of both feet will be taken according to a standardized protocol [24], and health-related quality of life will be assessed by using the 36-Item Short Form Health Survey (SF-36) and the 3-Level EuroQol Quality of Life Scale (EQ-5D-3 L) questionnaires.

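### The cost-utility analysis names no adjustment of the QALY difference for baseline EQ-5D-3L utility, so precision available from data already collected is given up

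*Protocol article*

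**What the plan says.** Cost per QALY gained is one of the two primary outcomes (Outcomes). The Economic evaluation section sets out how it will be estimated:

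- **QALY per patient:** "This QALY will be calculated as the product sum of health utilities and the lengths of the periods in-between successive measurements". Missing assessments are filled by carrying the last observation forward.
- **Inference:** "group differences will be assessed by calculating the 95% confidence intervals after correction for bias and using accelerated non-parametric bootstrapping".
- **QALY sensitivity analyses:** the utility scoring algorithm and the discount rate.

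No covariate is named in the base case or in the sensitivity analyses.

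At baseline, "health-related quality of life will be assessed by using the 36-Item Short Form Health Survey", and the same sentence adds the EQ-5D-3L (Baseline assessment). Allocation follows that assessment. It uses minimization with center and gender as the only factors (Randomization and blinding). The EQ-5D-3L is then repeated every 3 months.

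**The concern.** Baseline utility is likely to be among the strongest predictors of a patient's 18-month QALY. Patients who start with a higher utility tend to stay higher, and anyone who returns no follow-up questionnaire has the baseline value carried across the whole period. The minimization does not balance it, so the arms can differ at baseline by chance. A comparison of mean QALYs without a baseline term keeps that chance difference in the estimate. It also leaves in the standard error the variance that baseline utility could explain.

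At stake is the precision of the denominator of a primary outcome, and how close the single realised estimate comes to the truth. If the choice is left open until the data are seen, a decision to adjust after finding an imbalance would be data-driven.

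**Working it through.** **Sample size first.** The plan states: "With α = 0.05 (two-sided), power 80%, and based on an intention-to-treat analysis". Its two rates are 44% under usual care and 28.6% under enhanced therapy (Sample size calculation). The pooled two-proportion formula without continuity correction, with mean proportion 0.363, gives

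n = [1.960 × √(2 × 0.363 × 0.637) + 0.8416 × √(0.44 × 0.56 + 0.286 × 0.714)]² / 0.154² = 1.8978² / 0.023716 = 151.9,

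so 152 per arm and 304 in total. The plan's figure is reproduced exactly. The article does not state the allocation ratio; 1:1 is what reproduces it. This N rests on ulcer proportions. The article gives no SD, expected effect or sample size for QALYs.

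**Assumed inputs, none in the documents.** Utility SD is 0.20–0.30. The correlation r between baseline utility and QALY is 0.5–0.8, with 0.3 as a low case. The SD of the QALY is taken as 1.5 × the utility SD. Discounting is ignored: at 1.5% it would change 1.5 years to 1 + 0.5/1.015 = 1.493.

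**Formulas, with 152 per arm.**
- SE of the baseline utility difference = SD × √(2/152)
- Shift in the QALY difference from a one-SE imbalance = r × 1.5 × SD × √(2/152)
- Unadjusted SE of the QALY difference = 1.5 × SD × √(2/152)
- Adjusted SE = unadjusted SE × √(1 − r²)

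| SD | r | SE, baseline difference | One-SE shift in QALYs | Unadjusted SE | Adjusted SE | Interval narrower by |
|---|---|---|---|---|---|---|
| 0.20 | 0.5 | 0.023 | 0.017 | 0.034 | 0.030 | 13% |
| 0.25 | 0.7 | 0.029 | 0.030 | 0.043 | 0.031 | 29% |
| 0.30 | 0.8 | 0.034 | 0.041 | 0.052 | 0.031 | 40% |
| 0.25 | 0.3 | 0.029 | 0.013 | 0.043 | 0.041 | 5% |

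**Against the expected gain.** The planned difference is 0.44 − 0.286 = 0.154. The expected QALY gain is 0.154 × utility loss per ulcer × ulcer duration in years, and the last two are again assumptions.
- Loss 0.10 for 0.5 year gives 0.154 × 0.10 × 0.5 = 0.0077. With SD 0.25 and r 0.5–0.7 the one-SE shift is 0.0215–0.0301, or 2.8–3.9 times that gain.
- Loss 0.05–0.20 and duration 0.25–1.0 year give gains of 0.0019–0.031. Widening the SD to 0.15–0.30 and r to 0.3–0.8, the ratio of shift to gain runs from about 0.25 (0.0077/0.031) to about 21 (0.0413/0.0019).

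**Bias, coverage and sign.** Simulation of 5,000 trials with normal data and normal-theory intervals (r 0.7, SD 0.25, true gain 0.0077):

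| Analysis | Mean estimate | SD of estimate | 95% coverage | Wrong sign |
|---|---|---|---|---|
| Unadjusted | 0.0067 | 0.043 | 94.9% | 43% |
| Adjusted for baseline utility | 0.0075 | 0.031 | 94.9% | 40% |

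Both means agree with 0.0077 within simulation error (0.043/√5000 = 0.0006 for the unadjusted mean).

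**The case against.** The strongest reply is that this reads an omission as a decision. The article never calls the comparison unadjusted, and the stated bootstrap works equally well on a regression-adjusted difference. A journal article condenses a fuller protocol, and the covariates of a QALY model are often left to an analysis plan that is not shown. That stands in part: nothing quoted is wrong or contradictory, and a fuller document may already contain the adjustment. But the section is specific about the QALY formula, missing data, interval method and sensitivity analyses. As published, that specification has no baseline term.

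Three stronger readings are tempting, and the documents support none of them.

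- **That the result would be biased or its interval invalid.** Under randomization it is neither. The interval already allows for chance baseline differences, and an imbalance carries over only in proportion to the correlation.
- **That the imbalance is several times the expected gain, so that baseline decides the sign of the ratio and adjustment cures this.** The multiple holds for mid-range assumptions only. Adjustment lowers the wrong-sign risk in the illustration from 43% to just 40%; the main problem there is a small effect against the remaining noise.
- **That the QALY formula is defective because it does not say which score covers each interval.** Over six 0.25-year intervals, carrying each score forward differs from linear interpolation by 0.125 × (final − baseline utility) per patient. If the arms differed by 0.02 in that change (an assumption), the QALY difference would move by 0.0025, against a standard error of 0.043 at SD 0.25. This is ordinary analysis-plan detail.

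**Conclusion.** The point holds as an improvement available at no cost to the estimator of a primary outcome, and not as an error in the plan. The gain is an interval for the QALY difference about 13–40% narrower if the baseline–QALY correlation is 0.5–0.8, and only about 5% narrower if it is 0.3. It also removes from the realised estimate a chance shift of about 0.017–0.041 QALY per one-SE imbalance. These sizes rest on an assumed utility SD of 0.20–0.30, the assumed correlations, a QALY SD of 1.5 times the utility SD, and equal arms of 152. Only the 304 behind the last comes from the article. No firm statement about the shift relative to the expected QALY gain is possible from the documents.

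**What to change.** Add to the Economic evaluation section, or confirm in the analysis plan before the data are seen, that:

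1. the incremental QALY is estimated by regression of QALYs on arm and baseline EQ-5D-3L utility, refitted in each bootstrap resample;
2. costs are taken from the same resampled patients, so that the pairing of costs and effects is kept;
3. the unadjusted QALY difference is reported as a sensitivity analysis.

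If an existing plan already says this, a sentence pointing to it is enough. The cost is wording only: baseline utility is already collected, the sample size stays at 304, and no new data are needed.

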#### Health-related quality of life and costs

For the cost-effectiveness and cost-utility analysis, the following data will be collected at 3-monthly intervals:Health-related quality of life will be assessed by asking participants to complete the EQ-5D-3 L questionnaire. These questionnaires will be sent to the participant’s home and returned after completion in an enclosed return-envelopeAt the same time-interval of 3 months, or in case a foot ulcer develops at monthly intervals, the participant is asked to complete the study-specified versions of the Institute for Medical Technology Assessment (iMTA) Productivity Cost Questionnaire (iPCQ) and the iMTA Medical Consumption Questionnaire (iMCQ) [27] to gather volume data on productivity loss, out-of-hospital use of health care resources (e.g., podiatrist, pedicure), and out-of-pocket expensesUse of intramural health care resources during the study will be obtained from the participants’ medical status

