### Withdrawal of participants

Participants can withdraw from participation in the study at any time for any reason if they wish to do so, and without any consequences for their normal care. The physician can decide to withdraw a participant from the study in case of urgent medical reasons. After withdrawal from the study, information on ulcer outcome at 18 months will be obtained from the participant’s medical record if the participant consents to this procedure. Ulcer outcome data from participants who die during the study will be based on outcome at the moment of death (last observation carried forward).

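### Missing EQ-5D utilities are completed only by last observation carried forward, for a QALY that belongs to a primary outcome, with no sensitivity analysis for missing data

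*Protocol article*

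**What the plan says.** The Outcomes section puts the QALY in a primary outcome: "The primary outcomes in this study are the cost (savings) per patient without a foot ulcer (i.e., cost-effectiveness) and per QALY gained (i.e., cost-utility"). The Economic evaluation section defines it: "This QALY will be calculated as the product sum of health utilities and the lengths of the periods in-between successive measurements". The next sentence gives the only rule for gaps: "In case of missing assessments, the last observation will be carried forward". On robustness, the section plans this: "Sensitivity analyses will be performed for different (Dutch and UK population-based) health-utility scoring algorithms used to derive QALYs", and it also varies the discount rate. Missing data are not among the items varied.

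Under Health-related quality of life and costs, "the following data will be collected at 3-monthly intervals", and the EQ-5D-3L goes by post: "These questionnaires will be sent to the participant’s home and returned after completion". The cost questionnaires have a denser schedule after an ulcer ("or in case a foot ulcer develops at monthly intervals"). The EQ-5D-3L is listed only at three months.

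Under Withdrawal of participants, ulcer status at 18 months is recovered from the medical record if the patient agrees. No such recovery is described for utilities. The same section says that ulcer outcome data from participants "who die during the study will be based on outcome at the moment of death (last observation carried forward"). The subject of that sentence is ulcer status, not utility.

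**The concern.** Carrying the last value forward assumes that utility stays constant from the last returned form until the next one, or until month 18 if none follows. The Background says that ulcers harm quality of life, so the assumption is weakest around the event that the intervention aims to prevent. A patient who ulcerates and misses the next form keeps the pre-ulcer utility through the ulcer. A patient who withdraws keeps the last utility for every remaining visit.

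The article chose this method; it is not a detail left open. It decides the QALY difference in a primary outcome, that difference is likely to be small, and no planned analysis would show how far the result depends on the choice.

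The rule also has no exception for deaths, which the article foresees. It does not say whether an assessment that falls after death counts as missing.

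**Working it through.** **The plan's own figure.** The Sample size calculation gives ulcer proportions of 0.44 and 0.286, two-sided α = 0.05 and power 80%. I assume 1:1 allocation. The mean proportion is 0.363.

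n per arm = [1.960 × √(2 × 0.363 × 0.637) + 0.842 × √(0.44 × 0.56 + 0.286 × 0.714)]² / 0.154² = 3.602 / 0.02372 = 151.9, rounded up to 152. The total is 304, as stated. The sample size is not at issue. It confirms the planned risk difference of 0.44 − 0.286 = 0.154.

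The article gives no figure for utility, disutility, ulcer duration, mortality or missing forms. Everything below rests on assumed values and is undiscounted.

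**Living participants**

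QALY gain from ulcers prevented = 0.154 × disutility × duration in years.

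- Central: 0.154 × 0.10 × 0.5 = 0.0077
- Low: 0.154 × 0.05 × 0.25 = 0.0019
- High: 0.154 × 0.20 × 0.75 = 0.0231

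If a share m of post-ulcer utilities is missing in both arms and replaced by pre-ulcer values, the gain is multiplied by (1 − m).

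- m = 25%: 0.0077 × 0.75 = 0.0058
- m = 50%: 0.0077 × 0.50 = 0.0039

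If enhanced therapy costs more and the QALY difference comes only from ulcers, cost per QALY is multiplied by 1/0.75 = 1.33 or 1/0.50 = 2 at the same incremental cost.

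The opposite error is possible. If the ulcer-time form is returned and the form after healing is not, the low value is carried forward and the ulcer loss is overstated. With more ulcers under usual care, that enlarges the apparent gain.

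**Deaths, if time after death were filled**

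Assume utility 0.7. A patient who dies at month 6 has lived 0.7 × 6/12 = 0.35 QALY. Filling to month 18 gives 0.7 × 18/12 = 1.05.

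With deaths spread evenly over 18 months, the mean time filled is 0.75 year. At 5% mortality an arm's mean rises by 0.05 × 0.7 × 0.75 = 0.026. Equal mortality in the two arms cancels in the contrast. Each percentage point of imbalance shifts the contrast by 0.01 × 0.7 × 0.75 = 0.005 (0.0045 to 0.006 for utility 0.6 to 0.8).

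**The case against.** **Size.** The shift in living participants is small beside sampling error. From the central case it is 0.0077 − 0.0058 = 0.0019 to 0.0077 − 0.0039 = 0.0038. If the QALY standard deviation is 0.2 to 0.4 (an assumption), the standard error with 152 per arm is SD × √(2/152) = 0.023 to 0.046, about 6 to 24 times the shift. A shift toward no benefit is also conservative for a superiority hypothesis. Both points stand, and they limit how serious this is. They do not remove it: the primary result is a ratio of estimates, for which a bias toward zero QALYs is not a safeguard, and the direction is not assured.

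**Missing forms.** Forms are due every three months, and every participant is telephoned at the same interval, so gaps may be few. That is fair. The calls are described as a crosscheck of the cost questionnaires and lesions, not as a way to recover the EQ-5D. That gaps concentrate in ulcerated patients is plausible but not shown. The Study design section limits follow-up after an ulcer to the cost analysis, which might suggest that EQ-5D forms stop. The quality-of-life section lists them among the data for the cost-utility analysis, so I do not rely on that reading.

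**Deaths.** A reader might infer that the protocol credits dead patients with further QALYs, and might cite the Withdrawal section in support. The documents do not support this. The Withdrawal rule concerns ulcer status only, and the Statistical analysis section treats unrelated death as a competing risk. The QALY is summed between successive measurements, of which a dead patient has no more, and nothing calls time after death missing. Patients judged unlikely to survive 18 months are excluded, and a fuller plan may set utility to zero. What remains is that the rule is unqualified and does not exclude deaths.

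**Bootstrap.** A reader might also infer that the bootstrap interval must be too narrow. That does not follow. The carried-forward QALY is a fixed function of each patient's own observed data, so resampling patients captures the sampling variance of that estimator. The problem is bias.

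**Conclusion.** The point holds at a moderate level and should be fixed before analysis. A single weak imputation rule governs the utility side of a primary outcome, and no missing-data sensitivity analysis is planned. The direction of bias is not fixed. With similar missingness in both arms and pre-ulcer values carried into ulcer time, an assumed gain of 0.0077 QALY would fall by a quarter or a half, in proportion to the share of post-ulcer utilities replaced. All of these sizes depend on assumed disutility, duration and missingness.

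The death issue is one of wording. It matters for the contrast only if time after death is filled and mortality differs between arms. A one- or two-point imbalance would then move the difference by about 0.005 or 0.011 QALY, similar in size to the effect sought. No defect in the handling of costs is shown.

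**What to change.** In the Economic evaluation section, replace the sentence on missing assessments with:

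> Utility is 0 from the date of death. Missing EQ-5D utilities in living participants are multiply imputed by arm, using baseline utility, neighbouring scores, ulcer status and dates, centre and sex, combined with the bootstrap. Last observation carried forward is a sensitivity analysis.

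The cost is modest extra programming, mainly to nest imputation and bootstrap. The inputs are already collected: utilities, ulcer assessments, and the centre and gender used in randomization. The article places the analysis after the last follow-up visit, so the wording can be settled before then. If a fuller analysis plan already sets utility to zero at death, a cross-reference is enough for that part.
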